### Medical Complications

The recording of adverse events will be restricted to psychological conditions. Formally, they are defined as any disorder classified by the International Classification of Diseases F00-F99 ("Mental and Behavioral Disorders").

A serious adverse event (SAE) is an adverse event that may occur at any time of the treatment phase or up to 6 months after end of treatment: results in death; is life-threatening; requires subject hospitalization or prolongation of existing hospitalization; results in persistent or significant disability/incapacity; is a congenital anomaly/birth defect

Changes in mental disorders according to ICD-10 F00-F99 will be specifically asked for in the CRF pages filled by the interviewer at the following time-points: after 25 session of treatment; twelve months after end of treatment.

Any AE (according to the study specific definition) reported by the subject or detected by the local investigator will be collected during the trial and must be documented in the CRF. ICD-10 will be used by the local investigator to code the event. The standard coding system for adverse events, MedDRA, has been reported to be inadequate in psychotherapeutic studies [26]. The clinical course of the AE will be followed until it has changed to a stable condition or until end of follow-up phase, whatever comes first.

In case of SAEs Ethics Committee (EC) and Data Safety Monitoring Board (DMSB) will be informed within 24 hours after the SAE becomes known.

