### Safety aspects

Safety parameters will comprise newly occurring psychiatric diagnoses (SCID-I) and all serious adverse events that are reported during and up to six months after treatment.

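### The serious adverse event definition inherits the F00-F99 limit on adverse events, so a serious event not recorded as a mental disorder, notably self-harm, is not reportable as written

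*Protocol article*

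**What the plan says.** All places are in the protocol article, under Methods/Design.

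- **Medical Complications, scope of adverse events (AEs):** "The recording of adverse events will be restricted to psychological conditions". The sentence after it turns this scope into a definition by ICD chapter: "Formally, they are defined as any disorder classified by the International Classification of Diseases F00-F99".
- **Medical Complications, SAE:** "A serious adverse event (SAE) is an adverse event that may occur at any time of the treatment phase", or within six months after it ends. The criteria are that the event "results in death; is life-threatening; requires subject hospitalization or prolongation of existing hospitalization", leads to lasting or significant disability, or "is a congenital anomaly/birth defect".
- **Medical Complications, collection:** the duty to document in the CRF covers "Any AE (according to the study specific definition) reported by the subject or detected by the local investigator". The local investigator assigns the ICD-10 code. Interviewers also ask about changes in F00-F99 disorders after 25 sessions and twelve months after treatment ends.
- **Medical Complications, expedited notice:** the ethics committee and the safety board are told of an SAE within 24 hours of its becoming known.
- **Safety aspects:** the safety parameters are new psychiatric diagnoses on the SCID-I and "all serious adverse events that are reported during and up to six months after treatment".
- **Secondary analyses:** SAEs and drop-outs are summarised descriptively.

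**The concern.** Limiting ordinary adverse events to psychological conditions is a stated choice in a psychotherapy trial and is not at issue. The difficulty is that the SAE is built on the limited term. An act of self-harm is an event, not a disorder. Whether it counts as an SAE then depends on whether the local investigator records an F00-F99 diagnosis as the event. Self-harm is clearly relevant in this trial, since Table 1 excludes patients at prominent risk of it.

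Two things hang on the definition. The first is the 24-hour notice, which is the only rapid safety route the article describes. The second is the descriptive SAE summary, the only place where serious events would be set out by treatment group. With three sites coding locally, the wording also leaves room for similar events to be handled differently, although nothing in the article shows that this would happen.

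**Working it through.** No calculation decides this point. The check is to substitute one definition into the other and then look for another route by which a serious event could be reported.

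**Step 1: substitution (Medical Complications).**
- Recorded AE = an F00-F99 disorder.
- SAE = an AE in the stated time window that meets at least one seriousness criterion.
- Hence SAE = an F00-F99 disorder in that window that meets at least one seriousness criterion.

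The CRF duty refers back to the study-specific AE definition, which confirms that the narrow definition is the working one.

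**Step 2: test each criterion against the restriction.**

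| Criterion | Can an F00-F99 disorder meet it? |
|---|---|
| Results in death | Yes: death is an outcome that a mental disorder can have |
| Life-threatening | Yes |
| Hospital admission or longer stay | Yes, for example admission for a depressive episode |
| Lasting disability or incapacity | Yes |
| Congenital anomaly or birth defect | No |

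Four of the five criteria fit the restriction. The fifth can never be met under it. Either the list was meant to reach beyond F00-F99, in which case making the SAE a kind of AE is wrong, or the restriction holds and that criterion is empty. The text does not say which.

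**Step 3: look for another route for a serious event not recorded as an F00-F99 disorder.**
- *AE entry in the CRF:* tied to the study-specific definition, so none.
- *Scheduled interviewer questions:* they concern changes in F00-F99 disorders only, so none.
- *24-hour notice:* triggered by an SAE, so none.
- *Safety aspects:* the two parameters are new psychiatric diagnoses and SAEs, and such an event is neither.
- *Secondary analyses:* SAEs and drop-outs are described. A patient who left the trial because of such an event could appear as a drop-out, but the event would not be shown as a safety event.

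**Step 4: what is captured and what is not.**

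| Serious event | SAE as written? |
|---|---|
| New or worsened mental disorder leading to death, admission or disability | Yes |
| Self-harm or suicidal act recorded through an accompanying mental disorder | Yes, through that disorder |
| Self-harm or suicidal act with no F00-F99 disorder recorded as the event | No |
| Serious somatic event, such as an accident or surgery | No |

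**Step 5: scale.** Participants plans 105 patients. Assuming an even split, which is not guaranteed because therapists and not patients are randomised, each arm has 105 / 2 = 52.5 patients. One patient with an event is then 1 / 52.5 = 1.9 percentage points of an arm. This shows how much one missing event weighs in a descriptive table. It says nothing about how many would be missing, because the article gives no event rate.

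**The case against.** The strongest reply is that the restriction is deliberate, the gap is small, and some readings of it go too far.

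- **Deaths and admissions in general go unreported.** A reader might infer this, but the documents do not support it. The criteria describe what an event leads to, and a mental disorder can lead to death, threat to life or admission. Such events are SAEs as written. The death criterion therefore does not conflict with the restriction.
- **Safety aspects contradicts Medical Complications by promising all SAEs.** This does not hold either. Safety aspects uses the same defined term, and all SAEs is compatible with any definition of an SAE. For the same reason it does not close the gap.
- **The restriction is explained.** Medical Complications does give a reason for using ICD-10 and not MedDRA, but that concerns the coding system. It gives no reason for leaving out serious events.
- **Self-harm will usually be picked up.** Every patient has social phobia as primary diagnosis, comorbid disorders are allowed, patients at prominent risk of self-harm are excluded, and AEs reported by the patient or detected by the investigator are collected. Self-harm with a new or worsened disorder is reportable through it. This stands, and it narrows the gap to self-harm with no such disorder recorded and to somatic events. The somatic events say little about trained versus untrained therapists.
- **The intent may have been broader.** The congenital anomaly criterion suggests so. But the sites must apply the words, and the words put the SAE inside the AE.
- **The full protocol may define it differently.** It was approved by an ethics committee and commits to GCP, and it is not shown. The point, however, is not that a detail is missing: the article states the definition outright, and the stated definition is defective.

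**Conclusion.** The point holds in a limited form. As written, an SAE must be an F00-F99 disorder. A serious event not recorded as one, above all self-harm or a suicidal act coded outside that chapter, is lost to the 24-hour notice and to the descriptive SAE analysis. The congenital anomaly criterion is the one internal inconsistency, and it shows that the AE and SAE definitions were not fitted to each other.

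The number of events affected cannot be derived from the article and may well be small. The primary outcome, the sample size and the efficacy analysis are unaffected. The conclusion rests on reading the definitions literally and on the article reflecting the operative text. It should be corrected because the events at risk matter for safety and the correction costs little.

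**What to change.** In Medical Complications, keep the F00-F99 limit for non-serious adverse events only. Define an SAE separately, as any untoward event in the stated window that meets one of the listed seriousness criteria, whatever its ICD-10 chapter. State that the CRF duty, the 24-hour notice and the descriptive analysis follow this definition, and have Safety aspects use it. The congenital anomaly criterion then has a meaning. Naming self-harm and suicidal acts as examples would help sites code alike, but it is optional once the definition is separate.

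The cost is a rewording, a small CRF change and a few more SAE reports, some of them somatic events unrelated to the treatment. No change to design, sample size or efficacy analysis is needed.

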### Participants

Patients' inclusion and exclusion criteria are listed in table 1. According to these criteria, the sample of patients included in the study is representative for patients suffering from social phobia who qualify for treatment in an outpatient setting. No subject will be allowed to enrol in this trial more than once. Over a period of three years, a total of 105 patients are planned to be enrolled in the study (35 patients in each centre). A minimum number of 84 completers is intended.

**Table 1 T1:** Inclusion and exclusion criteria

Inclusion criteria	Diagnosis of SP (SCID-I [8]) and Liebowitz Social Anxiety Scale >30 (>60 for generalized subtype) [9] age: 18 to 70 years SP must be primary diagnosis (most severe disorder according to ADIS-IV) SP patients with comorbid disorders will be included, provided that SP is the primary diagnosis, thus ensuring a clinically representative sample as well as analyses of subgroups (e.g. type of SP, patients with comorbid depressive disorder) Informed consent.
**Exclusion criteria**	psychotic disorder prominent risk of self-harm acute substance related disorders personality disorders except for cluster C: avoidant, obsessive-compulsive or dependent personality disorder (SCID-II) organic mental disorder severe medical conditions concurrent psychotherapeutic treatment psychopharmacological treatment (stable medical treatments; e.g. SSRI without dose adaptation are permitted)

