#### Secondary analyses

Self-report questionnaires and observer ratings (SPAI, CGI, BDI, FSKN, DKB-35, CDS, BSSS, EQ-5D, HAQ, treatment adherence) will be analysed by mixed models with repeated measurements. Further analyses will include

• cross-sectional analyses comparing therapists;

• subgroup analyses of subjects' and therapists' conditions

• costs of the SP treatment (CSSRI)

All analyses will be conducted on a one-sided level of significance of 0.05. Descriptive statistics showing the measurements over time will be presented whenever appropriate.

Serious adverse events and drop-outs will be analysed descriptively.

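### The adverse event definition has no baseline reference, and non-serious worsening of social phobia or a baseline comorbid disorder is not a safety parameter

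*Protocol article*

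**What the plan says.** Four parts of the protocol article bear on this point.

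- **Medical Complications, definition.** Recording is restricted to psychological conditions: "Formally, they are defined as any disorder classified by the International Classification of Diseases F00-F99". A serious adverse event is an adverse event that also meets a seriousness criterion such as hospitalization.
- **Medical Complications, collection.** "Changes in mental disorders according to ICD-10 F00-F99 will be specifically asked for in the CRF pages filled by the interviewer", after 25 sessions and again twelve months after treatment ends. Any event under the study's own definition must be documented.
- **Safety aspects.** "Safety parameters will comprise newly occurring psychiatric diagnoses (SCID-I) and all serious adverse events", the latter during treatment and up to six months afterwards.
- **Secondary analyses.** The only safety analysis named is this: "Serious adverse events and drop-outs will be analysed descriptively".

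The population is set in Table 1 under Participants: "SP must be primary diagnosis", and "SP patients with comorbid disorders will be included, provided that SP is the primary diagnosis".

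**The concern.** Every patient already has at least one disorder of the kind that the definition covers, and some have more than one. In such a population an adverse event has to be judged against the state at entry. The definition does not say how. The list of safety parameters does refer to entry status, but only by counting new diagnoses. A patient whose social phobia, or whose comorbid depression, becomes clearly worse without meeting a seriousness criterion has no new diagnosis and no serious adverse event, and so does not appear among the safety parameters.

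This kind of harm is plausible here. The Interventions section adds encouragement to face feared situations to the manual, and comorbidity is admitted on purpose. If the arms differed in how many patients deteriorated, the stated safety parameters would not show it. There is also a risk of uneven recording: local investigators at three sites detect and code the events, and the text does not tell them whether worsening of an existing disorder counts.

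**Working it through.** No formula or sample size enters, and the plan states no figure to reproduce. The check sets the passages side by side for each course that a patient might take after entry.

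| Course after entry | Adverse event under Medical Complications? | Safety parameter under Safety aspects? | Covered by the interviewer's question on changes? | Named for safety analysis under Secondary analyses? |
|---|---|---|---|---|
| New disorder, not serious | Yes | Yes | Yes | No |
| Baseline comorbid disorder worsens, not serious | The disorder is in the category; worsening not addressed | No | Yes | No |
| Social phobia worsens, not serious | The disorder is in the category; worsening not addressed | No | Yes | No |
| Worsening that meets a seriousness criterion | As above | Yes, if worsening counts as an adverse event | Yes | Yes, on the same condition |
| Improvement or remission | Not addressed | No | Yes; the text gives no direction | No |

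Rows two and three are the gap: the change can be recorded, but it is neither a safety parameter nor named for analysis. Row one shows a smaller mismatch, since new diagnoses are a safety parameter that the analysis section does not name. Row four shows that the serious adverse event rule inherits the silence: whether hospitalization for a worsened baseline disorder qualifies depends on whether worsening is an adverse event, which the wording permits but does not state.

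Next, do the efficacy analyses show the same information?

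1. *Primary endpoint.* Remission is LSAS ≤30, and Table 1 requires LSAS >30 at entry (>60 for the generalized subtype). Let a patient enter at L0 > 30. If the score stays at L0 or rises to L0 + k with k > 0, the final value is above 30 either way, so both patients are non-remitters. Drop-outs are also counted as non-remitters. The endpoint cannot separate worsened, unchanged and lost patients.
2. *Repeated-measures models of LSAS, BDI and CGI.* These compare group means. If one patient improves by k and another worsens by k, the mean change is (−k + k)/2 = 0, the same as for two unchanged patients. A mean can therefore hide individual deterioration.
3. *Direction of testing.* The primary alternative is superiority of the manualized arm, and all analyses are one-sided at 0.05, so the tests are aimed at benefit.

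The scales hold the information needed, but no analysis named in the article counts patients who got worse.

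**The case against.** The best case for the plan has five parts.

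- **The texts have different jobs.** One sentence defines the category of condition to be recorded, one lists the safety parameters, and one is a data-collection prompt. A reader might infer three competing adverse event rules, or no definition at all. The article does not support that: a definition exists, and what it lacks is a baseline reference.
- **The literal reading is unrealistic.** A reader might infer that every patient has an adverse event on enrolment. But the same section speaks of events reported or detected, collected in the course of the trial and followed until they stabilize. That describes something arising or changing, and no investigator would log the inclusion diagnosis. This objection stands in full.
- **Worsening is not lost.** It can be recorded as a change, it can count if serious, and average severity is followed on LSAS, BDI and CGI. So it would be wrong to say that deterioration can be seen only as a serious adverse event. This stands too, but group means do not count deteriorated patients.
- **An article condenses a longer protocol.** Which safety tables are produced is commonly settled elsewhere. This weakens the point about the Secondary analyses section taken alone. It does not answer the rest: the article gives a definition that it calls formal, relies on it for documentation, and sets out a list of safety parameters that leaves non-serious worsening out.
- **Harm is not anticipated.** The sample size section says so, and no deterioration rate is given. That limits what can be said about size. It is not a reason to leave deterioration out of the harm comparison.

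**Conclusion.** The point holds as a gap in how harm is defined and reported. The formal definition does not refer to the pre-treatment state in a population where everyone enters with a qualifying disorder. The safety parameters, as worded, exclude non-serious worsening of social phobia or of baseline comorbidity, and none of the named efficacy analyses counts the patients who deteriorated.

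Its size cannot be given as a number of events. The effect is on the safety comparison only; the primary hypothesis, its test and the sample size do not change. The correction should be made because it is cheap and makes the harm comparison more informative, not because the trial's main result is at risk.

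The conclusion rests on two assumptions: that the article's wording on safety aspects matches the full protocol, and that worsening of an existing disorder is not treated there as a newly occurring diagnosis. If the full protocol already defines worsening and reports it, only the article's wording needs aligning.

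**What to change.** Reconcile Safety aspects, Medical Complications and the safety sentence in Secondary analyses around one definition:

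- An adverse event is the new onset or the worsening, relative to the pre-treatment assessment, of any F00-F99 disorder, social phobia included. Improvement is not an adverse event.
- In Safety aspects, extend the diagnostic parameter from newly occurring to newly occurring or worsened disorders.
- In Secondary analyses, add these events to the descriptive safety analysis, by arm. Beside them, give the number of patients in each arm whose LSAS or BDI worsened from baseline, with the rule for worsening fixed before the data are examined.

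The CRF is not shown, so check whether the answer to the question on changes can be separated into worsening and improvement; the definition needs that distinction. LSAS and BDI are already outcomes of the trial, so no new instrument or visit is needed, provided BDI is taken before treatment, as its repeated-measures analysis implies. The cost is wording, more non-serious events to record and one more descriptive table.

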### Ethical issues

The final study protocol and the final version of the written informed consent form were approved by the Ethics Committee of the Federal State of Rhineland Palatine (Germany), which is responsible for the Principal Investigator (Ref. No. 037.249.10 [7258]).

The procedure set out in this protocol, pertaining to the conduct, evaluation, and documentation of this trial, were designed to ensure that all persons involved in the trial abide by Good Clinical Practice (GCP) and the ethical principles described in the current revision of the Declaration of Helsinki. The trial will be carried out in keeping with local legal and regulatory requirements.

Before being admitted to the clinical trial, patients must consent to participate after the nature, scope, and possible consequences of the clinical trial have been explained in a form understandable to them. The patients must give written informed consent to participate in the study including their consent to publish.

## Discussion

The study is designed as an extension to the larger multi-site project in which Cognitive-Behavioral Therapy (CBT) and Short Term Psychodynamic Psychotherapy (STPP) of Social Phobia based on SET have been evaluated [7]. It combines the benefits of randomized controlled trials and naturalistic studies. We will ascertain to what degree practitioners integrate the new methods into their clinical routine. Furthermore, the study will determine whether the new methods lead to an improvement of treatment course and outcome and also whether the treatment effects of manualized STPP in routine psychotherapeutic treatment are comparable to those of the controlled, strictly manualized treatments of the main study. This study estimates potential reductions of treatment duration and costs by implementation of treatment manuals into clinical practice.

In contrast to the previous RCT in this study the patients are not recruited by the participating centres. Patients will seek treatment in the regular way of the German health care system attending private practitioners. Therefore, participating therapists recruit patients and announce them to the study centres. In the previous RCT treatments were limited to 25 sessions. In our study therapists are completely free to determine treatment duration. Accordingly, we determined primary outcome after 25 sessions. Our comparison group is naturalistically treated with standard psychodynamic psychotherapy without any additional training of the therapists.

Examinations of these issues in a methodologically rigorous manner will be of high relevance not only for the domain of social phobia but for the dissemination of innovative psychotherapeutic treatments in general.

Implementing the best obtainable treatment into the practice of experienced psychotherapists can be expected to increase treatment effectiveness. While evidence for the efficacy of Supportive Expressive Psychotherapy (SET) and other variants of Short Term Psychodynamic Psychotherapy (STPP) has accumulated [22,23], there has been a lack of studies on the transfer of manualized treatments to routine psychodynamic practice. Our study will be the first one to directly examine the effects of an additional training in a manualized and highly effective STPP procedure on outcome in routine psychotherapy for social phobia.

